## Abstract

**Background:**

Alcohol Use Disorder is a highly prevalent mental disorder which puts a severe burden on individuals, families, and society. The treatment of Alcohol Use Disorder is challenging and novel and innovative treatment approaches are needed to expand treatment options. A promising neuroscience-based intervention method that allows targeting cortical as well as subcortical brain processes is real-time functional magnetic resonance imaging neurofeedback. However, the efficacy of this technique as an add-on treatment of Alcohol Use Disorder in a clinical setting is hitherto unclear and will be assessed in the Systems Biology of Alcohol Addiction (SyBil-AA) neurofeedback study.

**Methods:**

*N* = 100 patients with Alcohol Use Disorder will be randomized to 5 parallel groups in a single-blind fashion and receive real-time functional magnetic resonance imaging neurofeedback while they are presented pictures of alcoholic beverages. The groups will either downregulate the ventral striatum, upregulate the right inferior frontal gyrus, negatively modulate the connectivity between these regions, upregulate, or downregulate the auditory cortex as a control region. After receiving 3 sessions of neurofeedback training within a maximum of 2 weeks, participants will be followed up monthly for a period of 3 months and relapse rates will be assessed as the primary outcome measure.

**Discussion:**

The results of this study will provide insights into the efficacy of real-time functional magnetic resonance imaging neurofeedback training in the treatment of Alcohol Use Disorder as well as in the involved brain systems. This might help to identify predictors of successful neurofeedback treatment which could potentially be useful in developing personalized treatment approaches.

**Trial registration:**

The study was retrospectively registered in the German Clinical Trials Register (trial identifier: DRKS00010253; WHO Universal Trial Number (UTN): U1111–1181-4218) on May 10th, 2016.

## Background

Alcohol use disorder (AUD) is characterized by drinking of alcohol despite negative or harmful consequences, a loss of control over drinking behavior, the development of craving for alcohol, and the occurrence of withdrawal symptoms. AUD puts a severe burden on individuals, families, and societies [1] and is highly prevalent in western countries with a twelve-month prevalence of 13.9% in the United States [2] and around 7% in Europe, where prevalence differs over a wide range between countries [3].

More than 80% of people suffering from AUD do not receive formal treatment [2], and of those who do, only 25–43% remain abstinent [4, 5]. To increase the efficacy of AUD treatment, novel treatment approaches are needed which would optimally be designed as modules that can flexibly be administered in personalized multimodal treatment programs.

The progress of basic neuroscientific knowledge about alcohol addiction and advances in methodology now make neuroscience-based treatment approaches like transcranial magnetic stimulation (TMS) [6–9], transcranial direct current stimulation (tDCS) [10–13], deep brain stimulation (DBS) [14, 15], and real-time functional magnetic resonance neurofeedback (rtfMRI NFB) [16–18] available, which are able to target disease-related brain regions and brain processes with more or less precision.

One process that has prominently been linked to AUD and is a promising aim for targeted neuroscience-based interventions is the cue-reactivity response [19–22], the reaction to the presentation of alcohol-related stimuli, e.g. pictures, odors, or taste of alcoholic beverages. In the brain, core regions associated with cue-reactivity are the ventral striatum (VS), the anterior cingulate cortex (ACC), and the ventromedial prefrontal cortex (vmPFC) [23, 24].

Reviewing the cognitive neuroscience literature on behavioral change in AUD, Naqvi & Morgenstern [25] concluded that enhanced reactivity of the ventral striatum to alcohol and alcohol-related cues together with impairments in prefrontal control regions are the major factors responsible for maintaining AUD. Along these lines, Becker et al. [26] have recently demonstrated enhanced striatal reward sensitivity and impairments in prefrontal-striatal connectivity in patients with AUD in a monetary reward task, hinting at a more generalized impairment in reward processing in AUD, which has also been found being predictive for neural changes during psychotherapeutic treatment [27].

To target the cortical and subcortical processes involved in cue-reactivity and cognitive control, real-time fMRI Neurofeedback is a promising approach. In rtfMRI NFB participants are shown a near real-time feedback signal indicating a specific brain process while they are lying in an MR scanner and are instructed to influence this feedback signal in a desired direction (see Fig. 2 for an illustration). In contrast to other treatment approaches like pharmacological interventions, TMS, or DBS, in rtfRMI NFB patients are actively engaging to influence a brain process, which might have additional psychological therapeutic benefits by promoting self-efficacy and self-regulation [28]. Furthermore, in comparison, rtfMRI NFB offers a relatively high spatial acuity, especially in subcortical brain regions.

While rtfRMI NFB treatment is a relatively new tool in psychiatry, first results are promising. Initial evidence has been presented that rtfRMI NFB has effects for example in major depressive disorder [29–34], schizophrenia [35–37], attention deficit hyperactivity disorder [38, 39], phobia [40], autism [41], posttraumatic stress disorder [42], and Borderline personality disorder [43].

With regard to substance use disorders, rtfMRI NFB has been mainly explored in the treatment of nicotine addiction [44]. Several studies have demonstrated a reduction of nicotine craving through NFB [45–48]. Interestingly, a recent study has found that including functional connectivity information in the feedback signal leads to a higher reduction of nicotine craving [49].

So far, only few studies have been conducted to assess the use of rtfRMI NFB as an interventional tool in AUD. Showing that neurofeedback training with feedback from individually chosen cortical regions was able to reduce craving in patients with AUD directly after neurofeedback training, Karch et al. [50] demonstrated the feasibility of neurofeedback interventions in AUD. In a study with non-treatment seeking heavy social drinkers, Kirsch et al. [18] found that participants who received real feedback in comparison to a yoked feedback group and a sham control group were able to learn to downregulate their ventral striatum activation during presentation of pictures of alcoholic beverages. They could further show that downregulation of the VS was correlated with activation in the right inferior frontal gyrus in the real feedback group, which is in accordance with the model of Naqvi & Morgenstern [25].

In the Systems Biology of Alcohol Addiction (SyBil-AA) rtfRMI NFB study we are now testing whether neurofeedback training will have beneficial effects in heavily impaired AUD patients in a clinical setting. The results of this study will provide insights into the efficacy of NFB training in AUD, the involved brain systems, and might help to identify predictors of treatment success which could potentially be useful in developing personalized treatment approaches.

## Methods/Design

To investigate the effect of rtfMRI NFB and identify the underlying neural mechanisms we will include *N* = 100 patients with a diagnosis of alcohol use disorder recruited from the outpatient and inpatient clinics of the Department of Addiction Behavior and Addiction Medicine at the Central Institute of Mental Health (CIMH), Mannheim, Germany. Participants will be randomly assigned to one of 5 parallel groups. All groups will receive true rtfMRI NFB from different brain processes and will be followed up monthly for three months (Fig. 1).

**Fig. 1 Fig1:**
[figure not shown]
Study flow chart. *N* = 100 patients with a diagnosis of alcohol addiction from the local inpatient and outpatient addiction clinics are randomized to 5 single-blind groups, receive rtfMRI NFB treatment on 3 days within two weeks, and are followed up monthly for 3 months

### Participant eligibility and recruitment

Eligible participants are between 18 and 65 years with normal or corrected-to-normal vision. They are diagnosed with alcohol dependence according to the International Classification of Diseases, tenth edition (ICD-10: F10.2) with controlled abstinence for at least 5 and a maximum of 21 days prior to study inclusion. Additionally, a medically supervised detoxification program (treatment of withdrawal symptoms with short-acting benzodiazepines or clomethiazole) has to have been completed for at least 3 days.

Exclusion criteria are: meeting the criteria of any axis I psychiatric disorder according to the Diagnostic and Statistical Manual of Mental Disorders, fourth edition (DSM-IV) and the ICD-10 within the past 12 months, with the exception of alcohol and nicotine abuse/dependence and a mild depression related to alcohol consumption or detoxification. Further exclusion criteria are a positive urine drug screening, current use of psychotropic or anticonvulsive medications, epilepsy or neurological or severe medical illness, suicidal tendencies, pregnancy, and breastfeeding.

For recruitment, participants are informed by a psychologist of the study team about the study purpose and are able to ask all questions concerning the study content. Participants are then asked to provide written informed consent before being screened for in- and exclusion criteria. Participants are able to withdraw their consent at any time.

### Screening assessment & group allocation

Screening for in- and exclusion criteria includes the Structured Clinical Interview for DSM-IV (SKID-I) [51] conducted by a clinical psychologist. Either during the detoxification program or the screening assessment a drug and pregnancy test is conducted. Please see Table 1 for further information on the schedule of measurements.

**Table 1 Tab1:** Schedule of measurements conducted in the study

Measurement	S^a^	T0^a^	MRI1^a^	MRI2^a^	MRI3^a^	FU1/2^b^	FU3^a^
Sociodemographic information		X					
Structured Clinical Interview (SKID – I)	X						
Drinking Assessment Interview (Form 90)		X					
Blood sample (AUD-related markers)	X						X
Urine sample (pregnancy, drugs)	X						
Current medication	X					X^c^	X^c^
Current smoking behavior		X^c^	X^c^	X^c^	X^c^	X^c^	X^c^
Breath alcohol test							X
Current drug use						X^c^	X^c^
Incentive Conflict Task		X					
Clinical & Personality Questionnaires							
Edinburgh Inventory of Handedness	X						
Beck Depression Inventory		X					
State Trait Anxiety Inventory		X					
Behavioral Inhibition/Approach System		X					
Barratt Impulsiveness Scale		X					
Fagerstrøm Test of Nicotine Dependence		X					
Alcohol-Related Questionnaires							
Quick Drinking Assessment Interview (Form 90-AQ)						X	X
Alcohol Dependence Scale		X					
Alcohol Abstinence Self-Efficacy Scale		X			X		X
German Inventory of Drinking Situations		X					
Obsessive Compulsive Drinking Scale		X			X		X
Alcohol Urge Questionnaire		X			X		X
Craving-Automatized-Scale-Alcohol		X			X		X
MRI							
Anatomical image (MPRAGE)			X	X	X		
Resting state			X	X	X		
Neurofeedback			X	X	X		
Transfer run			X		X		
Craving (visual analog scale) pre & post scanning			X	X	X		
Perceived control over NFB (visual analog scale)			X	X	X		

*S* screening assessment, *T0* baseline assessment, *MRI* rtfMRI scanning days, *FU* monthly follow-up. ^a^face-to-face; ^b^via telephone; ^c^self-reported (if unclear)

Participants who meet inclusion criteria are randomly assigned to one of five groups: three experimental and two control groups, respectively. Each group has to fulfil different tasks with either downregulating the ventral striatum, upregulating the right inferior frontal gyrus (rIFG), increasing the connectivity (negative correlation) between rIFG and VS, downregulating the auditory cortex (downregulation control) or upregulating the auditory cortex (upregulation control). The auditory cortex was chosen as control region because it is not involved in cue-reactivity [22].

Group allocation of included participants is conducted by the study team with a computer-generated random list based on the sequence of inclusion. No stratification factors are used in the allocation process.

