### Baseline assessment

After group allocation, all participants take part in a baseline assessment about demographic questions, alcohol use, actual medication, personality, and clinical symptoms (see Table 1). In addition, participants conduct the computer-based Incentive Conflict Task (ICT, [52]) during the baseline assessment.

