### Follow-up assessments

Follow-up assessments take place monthly after the last MRI session over a period of three months. At the first two time points participants are contacted by phone and asked about their current medication, their abuse of tobacco, nicotine and drugs and a potential alcohol relapse (see Table 1). Three months after the last MRI session, patients are invited to a final appointment at the CIMH. During this session, blood samples are collected and participants are asked about substance use and answer alcohol-related questionnaires (see Table 1). For the final appointment, patients receive a monetary compensation of 50 €.

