There are some shortcomings of the protocol. First, the study is only single-blind. The staff members must prepare the individual feedback set up (definition of ROI, definition of direction) and are therefore not blinded. In future studies, a double-blind protocol could be implemented by separating staff that prepares the individual NF setup and staff that instructs the participants. However, we think it is worth to test the general applicability of rtfMRI NF to AUD patients before setting up such an extensive study protocol. Second, the study was retrospectively registered in the German Clinical Trials Register (DRKS00010253; WHO Universal Trial Number (UTN): U1111–1181-4218). Due to fast inclusion of the first patient, registration was conducted shortly after the begin of the study, but before any data was processed or analyzed (Inclusion of first patient: 03/30/2016; application for registration: 04/26/2016; registration date: 05/10/2016). However, the registration complies with the goals of the study described in the grant proposal and the study protocol will not be altered during the study. Finally, we have not defined stopping criteria, because we do not expect side effects besides those that can be expected from fMRI scanning, which is a safe and well-established technique. However, the principle investigators will decide whether to continue or terminate the study or specific parts of it if side effects were reported by the participants.

Overall, the study is well suited to provide valuable data on the efficacy of rtfMRI NFB as an add-on treatment for AUD in a clinical setting. Furthermore, the large amount of imaging data collected on the three scanning days will be helpful to better understand how rtfMRI NFB is working, and to identify factors that predict its clinical effects and could potentially be useful for developing personalized treatment approaches.

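### Baseline drinking is taken by interview after group allocation in a trial with unblinded staff, which can bias any change-from-baseline analysis of alcohol intake

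*Protocol article*

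**What the plan says.** The section on screening and group allocation describes who allocates and how: "Group allocation of included participants is conducted by the study team with a computer-generated random list based on the sequence of inclusion". Patients who pass screening are allocated at this point.

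The section on the baseline assessment fixes what comes next: "After group allocation, all participants take part in a baseline assessment about demographic questions, alcohol use, actual medication, personality, and clinical symptoms". Table 1 lists the content of this visit (T0, face-to-face). It includes the Form 90 drinking interview, the dependence scale, the craving scales and the abstinence self-efficacy scale.

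The Discussion names single blinding as a shortcoming and gives the reason: "The staff members must prepare the individual feedback set up (definition of ROI, definition of direction) and are therefore not blinded".

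The section on statistical analyses makes relapse (by survival analysis) and reduced alcohol intake over follow-up the primary outcome. For months 1 and 2 the article says: "At the first two time points participants are contacted by phone and asked about their current medication", and relapse is asked about in the same call. For month 3 it says: "During this session, blood samples are collected and participants are asked about substance use and answer alcohol-related questionnaires". Table 1 adds a breath alcohol test at that visit.

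**The concern.** A baseline value serves as a neutral reference only if group membership could not affect it. The usual way to guarantee this is to record it before anyone knows the group. Here the stated order is the reverse, and staff are stated to be unblinded. An interview about past drinking involves probing and judgement, so an interviewer who knows the group can, without intending to, record slightly more or less drinking in one group than in another.

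The stake is the intake component of the primary outcome. If intake is judged by its fall from T0, part of an apparent treatment effect could come from the starting value. The reason given for unblinding, preparing the feedback, belongs to the scanning days and does not explain why T0 has to follow allocation.

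**Working it through.** The plan states no figure on this point, so the check compares the stated steps and then follows a baseline error through the possible analyses.

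**Step 1: order of events.** Inputs: the sections on allocation and baseline, and Table 1.
- Screening (before allocation): diagnostic interview, AUD-related blood markers, urine tests, current medication, handedness.
- Allocation.
- T0 (after allocation): Form 90, dependence scale, craving scales, self-efficacy, other questionnaires, Incentive Conflict Task.
- MRI1 to MRI3, then follow-up.

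Form 90 is marked only at T0, and its short version only at follow-up. No intake measure is scheduled at screening. The blood markers are the only alcohol-related measurement marked there, and they measure intake at most indirectly.

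**Step 2: is allocation needed at T0?** Nothing listed at T0 differs by group. The allocation is first used when target region and direction are set up for MRI1. The order can therefore be reversed without affecting the intervention.

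**Step 3: which T0 items are exposed.** Form 90 is an interview held face-to-face and is the main exposed item. The craving, dependence and self-efficacy scales are listed as questionnaires, and the data management section has questionnaires scanned automatically. The Discussion describes patients as blind to experimental versus control status, though not to the direction of regulation. Staff knowledge has less of a route into these scales.

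**Step 4: effect on each analysis.** Let X be recorded intake at T0 and Y intake at follow-up. Let d be the difference in mean X between experimental and control patients that arises only because the interviewer knows the group.
- Reduction X − Y: the between-group difference shifts by d, one for one.
- Y adjusted for X with within-group slope b: the adjusted difference shifts by −b × d. Adjustment reduces the shift when b lies between 0 and 1, but removes it only if b = 0.
- Y compared directly: shift 0 from this source.
- Time to relapse without T0 as a covariate: shift 0 from this source.

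**Step 5: size of d.** The documents contain nothing from which d could be estimated. The power section assumes Cohen's d = .5 for follow-up measures and does not mention change scores, so it gives no scale for a baseline recording error either.

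**The case against.** Four counter-arguments deserve weight.

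1. The article names neither Form 90 nor a change score for reduced intake. This stands, and it makes the concern conditional. Still, Form 90 at T0 is the only scheduled pre-treatment intake measure from which a reduction could be computed.

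2. The lack of staff blinding is disclosed. This also stands, but the disclosure concerns feedback set-up. It does not mention that the baseline follows allocation.

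3. The article does not say who conducts T0, so an interviewer might in practice not know the group. That is possible, but nothing in the stated order or staffing ensures it.

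4. Enrolment began on 03/30/2016 and the article says that the protocol will not be altered. Changing the order midway would mix two kinds of baseline. This is a fair practical point and shapes the remedy for patients already enrolled.

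A reader might also infer that recruiting staff can foresee the next assignment, because a psychologist from the study team informs patients and the study team allocates from a sequential list. The text does not support that. A list used in order can still be concealed, nothing says that the recruiter sees it, and a condensed article commonly leaves concealment details to the full protocol.

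A reader might likewise conclude that the relapse outcome is biased. The article does not say who makes the follow-up calls, so only a possible exposure can be stated.

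**Conclusion.** The concern holds for the order of T0 and allocation. The article places the only pre-treatment intake interview after allocation, in a trial whose staff are unblinded, and gives no reason for that order. The consequence is a risk of bias in any analysis of intake as change from T0. It is not evidence that bias occurred. It rests on two assumptions: that the T0 interviewer may know the group, and that reduced intake will be measured against T0.

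The relapse survival comparison does not depend on T0, and the T0 questionnaires are less exposed. No numerical size can be given. Only the algebra is certain: a recording difference enters a change score in full.

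As a secondary note, the disclosed lack of staff blinding may also reach the relapse interviews at months 1 to 3. The first two are telephone self-report with no biological check in Table 1. The month-3 breath and blood tests provide a partial check, but they do not date a relapse for a survival analysis.

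**What to change.** - **Patients still to be enrolled:** complete all T0 assessments before that patient's allocation is opened. Only the order of two existing steps changes, with no new visit, test or patient. State the date of the change, so that baselines taken before and after allocation can be told apart.
- **Patients already enrolled:** report that T0 followed allocation. Do not rest the intake conclusion on change from T0 alone; also compare follow-up intake directly between groups. The price is some precision if T0 intake predicts later intake. This comparison avoids the baseline problem but not any interviewer influence at follow-up.
- **Secondary:** report the month-3 breath test and blood markers against self-reported abstinence, by group. Both are already scheduled, so the cost is one table. If follow-up interviewers are in fact unaware of the group, one sentence saying so would settle that part. Requiring blinded interviewers might call for the kind of staff separation that the authors consider too extensive for this study, so it is not made a condition here.

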### Statistical analyses

As primary outcome analysis we will conduct group comparisons of relapse rates with survival analysis and assess reduction of alcohol intake during the follow-up phase. As secondary and exploratory outcome measures we will assess whether rtfMRI NFB reduces alcohol craving during the NFB sessions, how brain activation and brain connectivity changes within and between the sessions, whether functional or structural MRI markers can be identified that predict neurofeedback learning and the success of the intervention, and whether differences in efficacy of the group-specific interventions do exist.

To analyze the effects of rtfMRI NFB, offline data analysis will be conducted with MATLAB and SPM. Data preprocessing will consist of slice-time correction, realignment, segmentation of the anatomical image, normalization to the MNI space, smoothing, and identification of outlier volumes with excessive head motion. The preprocessed data will be used in first level single subject analyses in which the time courses of the experimental conditions will be convolved with the canonical hemodynamic response function and used in a general linear model to estimate brain responses during rtfMRI NFB. Then, first level results will be used in second level group comparisons to estimate differential activation between groups, test for associations with clinical variables, and assess the predictive value of imaging markers for the future course of the disease. Additionally, large-scale adaptations in functional networks during rtfMRI NFB will be assessed by whole-brain psychophysiological interaction analysis [53].

Depending on the type of the data, missing data will either be left out from the analyses (e.g. fMRI data), or imputed (e.g. missing questionnaire items).

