### Power calculations

Power calculations were conducted with the G*Power software package [54]. In the clinical analysis (follow-up measures) the power for detecting group differences at *p* < .05 under the assumption of a medium effect size (Cohen’s d = .5) is 78% with two sample *t*-tests when treatment (*n* = 60) and control groups (*n* = 40) are pooled. Assuming an effect size of f = .61 as observed for the neurofeedback effect on VS reduction in our pilot study [18], the neurofeedback analyses based on an ANOVA repeated measures model with a group x time contrast has a power of 89% in the VS and of 88% in the rIFG to detect FWE (Bonferroni) corrected significant results in the respective ROI analyses.

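### Allocation is unstratified and no baseline covariate is named for the clinical comparison, so precision is forgone that ANCOVA on baseline drinking and a few pre-specified covariates could recover

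*Protocol article*

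**What the plan says.** All places are in the protocol article.

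- **Allocation** (Screening assessment & group allocation): patients go to five groups from a "computer-generated random list based on the sequence of inclusion", and "No stratification factors are used in the allocation process".
- **Population** (Methods/Design; Participant eligibility and recruitment): patients are "recruited from the outpatient and inpatient clinics of the Department of Addiction Behavior and Addiction Medicine", with "controlled abstinence for at least 5 and a maximum of 21 days prior to study inclusion". The mix of settings is not given.
- **Clinical analysis** (Statistical analyses): "As primary outcome analysis we will conduct group comparisons of relapse rates with survival analysis". Reduction of alcohol intake during follow-up is to be assessed as well. No covariate is named for either, and none is excluded.
- **Power** (Power calculations): for d = 0.5 the power of the follow-up comparison "is 78% with two sample *t*-tests when treatment (*n* = 60) and control groups (*n* = 40) are pooled". Sidedness is not stated.
- **Baseline data** (Table 1; Baseline assessment): the Form 90 drinking interview is taken at T0, after allocation and before the first scanning day. Form 90-AQ is taken at each follow-up.

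**The concern.** Days already abstinent, recent drinking and recruitment setting are plausible predictors of relapse and intake over three months. With no stratification, nothing in the design balances them. With no covariate named, nothing in the described analysis corrects an imbalance that arises or removes the outcome variation they explain.

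Two things are at stake. One is the precision of a clinical comparison whose stated power is only 78%. The other is how the single observed result reads if the pooled groups happen to differ at baseline.

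The Discussion says the protocol will stay unchanged during the study, so stratification will not be added later and adjustment in the analysis is the remaining remedy. It should be settled before outcomes are seen. The section on data management and dissemination plans interim analyses for presentation while data are still being collected, and covariates chosen after that would be open to the charge of data-driven selection.

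**Working it through.** **Inputs from the article:** n = 60 and 40 (pooled), d = 0.5, alpha 0.05, two-sample t-test, stated power 78%. **Assumed:** the correlation r between baseline and follow-up drinking, taken from 0.1 to 0.5, because the documents give none.

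**1. The plan's own figure.** The noncentrality is d × √(n₁n₂/(n₁+n₂)) = 0.5 × √(2400/100) = 0.5 × 4.899 = 2.449, with 98 degrees of freedom.

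- One-sided: critical value 1.661, power 78.5%. This reproduces the stated 78%.
- Two-sided: critical value 1.984, power 67.9%.

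The sidedness of the 78% is a separate matter. Both versions are carried forward.

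**2. ANCOVA on one baseline covariate.** The residual SD shrinks by √(1−r²), so the effective effect is 0.5/√(1−r²), with 97 degrees of freedom.

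| r | effective d | two-sided power | one-sided power |
|---|---|---|---|
| no covariate | 0.500 | 67.9% | 78.5% |
| 0.1 | 0.503 | 68.3% | 78.8% |
| 0.2 | 0.510 | 69.7% | 79.9% |
| 0.3 | 0.524 | 72.0% | 81.7% |
| 0.4 | 0.546 | 75.4% | 84.4% |
| 0.5 | 0.577 | 80.0% | 87.8% |

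**3. A change score as the alternative.** The article speaks of reduction of intake, which could be read as follow-up minus baseline. If both are on a common scale with equal SDs, and d = 0.5 is defined on the follow-up SD, the change score has SD √(2(1−r)). At r = 0.3 the effective d is 0.5/√1.4 = 0.423, and two-sided power is about 54%. ANCOVA gives 72.0% at the same r.

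**4. Chance imbalance without stratification.** The SD of a standardised baseline difference is √(1/60 + 1/40) = 0.204, so the 95% range is ±1.96 × 0.204 = ±0.40 SD. The chance of exceeding 0.3 SD in either direction is 14% per covariate.

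A baseline difference of b SD shifts an unadjusted outcome difference by about r × b. At the edge of the range this is 0.3 × 0.40 = 0.12 SD for r = 0.3 and 0.5 × 0.40 = 0.20 SD for r = 0.5, against an assumed effect of 0.5 SD.

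Steps 1 to 3 concern a continuous outcome. They say nothing directly about the survival analysis of relapse.

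**The case against.** The strongest reply is that the article states nothing wrong. Unstratified randomisation is a legitimate design and is openly reported. The term survival analysis includes Cox regression with covariates, and a covariate list is commonly left to the full protocol or SAP, which is not shown. The t-test appears only as the basis of the power calculation.

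Much of this stands, and it limits the point in four ways.

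- A reader might infer that the relapse comparison is planned as unadjusted. The documents do not say so; they are silent.
- A reader might infer that baseline drinking should have been a stratification factor. Under the present schedule it could not be, because the baseline assessment follows allocation.
- A reader might infer that chance imbalance biases the trial or raises its type I error. It does neither: randomisation already allows for it. It costs precision and can shift the single estimate.
- A reader might infer that the trial loses power it was promised. The 78% already assumes no covariate, so what is missing is a possible gain, and at r = 0.1 that gain is under one percentage point.

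The reply does not remove the narrower point. The only method the article attaches to the follow-up measures in its power section is a test without covariates, while the trial collects a pre-treatment drinking measure suited to ANCOVA. That is a better method available at almost no cost, not merely a detail left to another document.

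**Conclusion.** The point holds as an improvement that should be made, not as an error that invalidates the comparison. Allocation is explicitly unstratified, the clinical comparison is powered on plain t-tests, and no baseline covariate is named. For continuous intake, adjustment for baseline drinking would add between less than 1 and about 12 percentage points of two-sided power (67.9% to between 68.3% and 80.0%) for r from 0.1 to 0.5. One-sided, it would add up to about 9 points (78.5% to 87.8%). A change-score test could do worse than the plain t-test: about 54% two-sided at r = 0.3, under the scaling stated above. Chance imbalance in the pooled comparison lies within about ±0.40 SD per covariate in 95% of trials.

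The size of the gain rests wholly on the assumed correlation. The documents give no distribution of baseline drinking and no mix of settings, so how far patients differ on these can be judged only from the 5 to 21 day window and the two recruitment sources. No gain has been calculated for the survival analysis.

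**What to change.** Pre-specify the following before outcome data are examined, and before any interim presentation:

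1. **Intake:** ANCOVA of follow-up drinking on baseline Form 90 drinking, in place of a two-sample t-test or a test of change scores.
2. **Relapse:** a survival comparison, for example Cox regression, adjusted for a small fixed set of baseline factors: days abstinent at inclusion, baseline drinking, and recruitment setting if it is recorded (Table 1 has no row for it). Keep the unadjusted log-rank test as a supporting analysis.

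The allocation procedure need not change.

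The cost is a few sentences of analysis text and slightly more analysis work; Form 90 drinking is already scheduled and days abstinent are already checked for eligibility. One caution applies: the T0 interview follows allocation, and the Discussion says staff are not blinded, so knowledge of the group could influence it. Factors fixed at screening are the safer covariates. A sensitivity analysis that adjusts only for those would show whether the result depends on the T0 measure.
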